# The extended Infant Feeding, Activity and Nutrition Trial (InFANT Extend) Program: a cluster-randomized controlled trial of an early intervention to prevent childhood obesity

**DOI:** 10.1186/s12889-016-2836-0

**Published:** 2016-02-18

**Keywords:** Randomized controlled trial, Infant, Early-childhood, Obesity, Prevention, Intervention, Scalability, Feeding, Physical-activity, Screen-time

## Abstract

**Background:**

Understanding how we can prevent childhood obesity in scalable and sustainable ways is imperative. Early RCT interventions focused on the first two years of life have shown promise however, differences in Body Mass Index between intervention and control groups diminish once the interventions cease. Innovative and cost-effective strategies seeking to continue to support parents to engender appropriate energy balance behaviours in young children need to be explored.

**Methods/Design:**

The Infant Feeding Activity and Nutrition Trial (InFANT) Extend Program builds on the early outcomes of the Melbourne InFANT Program. This cluster randomized controlled trial will test the efficacy of an extended (33 versus 15 month) and enhanced (use of web-based materials, and Facebook® engagement), version of the original Melbourne InFANT Program intervention in a new cohort. Outcomes at 36 months of age will be compared against the control group.

**Discussion:**

This trial will provide important information regarding capacity and opportunities to maximize early childhood intervention effectiveness over the first three years of life. This study continues to build the evidence base regarding the design of cost-effective, scalable interventions to promote protective energy balance behaviors in early childhood, and in turn, promote improved child weight and health across the life course.

**Trial registration:**

ACTRN12611000386932. Registered 13 April 2011.

## Background

Childhood overweight and obesity are prevalent across developed and developing nations [1, 2]. While prevalence rates may be slowing in some countries [3], the prevalence of overweight and obesity in children in lower socioeconomic environments appears to have increased [4]. Childhood overweight and obesity remain high priorities for public health and it is imperative that we address prevention comprehensively, including through the design of programs that can be scaled up [5]. Key to scalability are issues of intervention dose (timing, intensity and duration) and the capacity to utilize existing infrastructures [6]; both will determine future cost, and hence, sustainability. Determining the minimal dose of intervention needed for sustained change to children’s obesity risk behaviours, and in turn body weight, underpins the rationale for this extended version of an established intervention embedded within existing health services in Victoria, Australia.

Similar to other developed nations [1], in Australia ~25% of children aged 2–17 are overweight or obese [7]. The expression of adiposity begins in early life with nearly 23% of Australian 2–4 years affected [7]. Overweight and obesity are recognized to have negative consequences for children’s health and wellness during childhood and through to adult life [8, 9]. Further, the timing of weight gain is considered important. Evidence highlights that rapid weight gain across the first two years of life is strongly predictive of later adiposity in both childhood and adolescence [10]. It is important therefore that we acknowledge both the early expression of overweight and obesity and that the early years provide a vitally important opportunity for prevention.

Obesity-promoting lifestyle behaviours are established early. For example, Australian [11, 12] and international data [13–15] report that from an early age children are consuming diets high in energy-dense foods/drinks and low in fruits and vegetables. Our own data from the Melbourne Infant Feeding Activity and Nutrition Trial (InFANT) Program of children aged 9 and 18 months of age showed the consumption of energy-dense, nutrient-poor foods occurs as early as nine months of age with 12% of dietary energy provided by non-core foods [16]. There is also evidence of high levels of sedentary behaviour in early childhood. For example, a systematic review found that the average duration of television viewing for children under the age of two years reported by studies ranged between half an hour and more than five hours per day [17]. Data from the Melbourne InFANT Program shows that television viewing increases across the early childhood period [18]. While little physical activity data exists for children under two years, our research shows that 19-month old children spend an average of 184 min in light-intensity physical activity and 47 min in moderate- to vigorous-intensity physical activity each day, with the remainder of their day spent sedentary [19].

The early establishment of obesity promoting behaviours is important both because they will determine weight gain trajectories but also because these behaviours are known to track. For example, there is evidence of tracking of children’s dietary [16, 20, 21] and physical-activity [22, 23] behaviours from childhood to adolescence and adulthood. Early childhood thus provides a unique and circumscribed opportunity in which we might reduce risk of lifetime adiposity; a time within which to seek to establish lifestyle behaviours that will promote health and minimize the risk of the development of obesity and associated co-morbidities throughout life.

Children’s eating, physical-activity and sedentary behaviours are learnt and sustained in the home and evidence from our own [24] and others’ studies suggest this environment may improve children’s weight and energy-related behaviours [25, 26]. Parents shape children’s emerging food and physical activity choices through a variety of means including: their knowledge regarding eating, physical activity and sedentary behaviours; parenting style and feeding style; modelling of eating/activity; the food/facilities made available and accessible; food portion sizes and the use of food as rewards [27].

Several existing randomized controlled trials (RCTs) report that parent-focused interventions from birth hold promise for early childhood obesity prevention, with trials reporting modest effects on early childhood weight [26], diet [24–26] and sedentary behaviours [24]. In addition, results from a prospective meta-analyses incorporating these RCTs (Early Prevention of Obesity in CHildhood (EPOCH) Trial *n* = 2196) provides further support for this focus on interventions in early life [28]. In that analysis, compared to controls, intervention children at age 18 to 24 months had a significantly reduced zBMI, were breastfed for longer, spent less time viewing television, and were significantly less likely to be exposed to a range of obesity-promoting feeding behaviours, specifically controlling feeding style, use of food as a reward, and pressure to eat [29].

However, while these pooled data showed important effects on zBMI, three of the four constituent studies have recently reported that there were no differences in zBMI between intervention and control groups at age five [30–32]. The prospective meta-analyses will be undertaken to confirm this loss of intervention effect over time when the last of the four trials [33] collects their 5-year old post-intervention data (2016). This potential failure to maintain intervention effect is perhaps not surprising given the complexity and the dynamic nature of the targeted energy-related behaviours across early childhood. The substantial developmental change occurring in the early years frequently heralds a particularly challenging period for parents. For example, parents report increased rejections of food and proposed limits to screen time [34] as their child moves through the toddler years. It is likely that parents will require ongoing support to develop strategies that can address the evolving challenges they face.

One of these RCTs, the Melbourne Infant Feeding Activity and Nutrition Trial (InFANT) Program (herein referred to as the Melbourne InFANT Program), informed the protocol for the current study, known as the InFANT Extend Program. The methodology employed for the Melbourne InFANT Program have been previously published [35]. In brief, the Melbourne InFANT Program was a cluster-randomized controlled trial of a community-based, early obesity prevention program, designed to be integrated into existing service delivery systems. The intervention comprised 6 × 2 h sessions delivered quarterly to first-time parents from when infants were approximately three months of age to approximately 18 months of age. Sessions were delivered within existing first-time parent groups, established by community Maternal and Child Health nurses (MCHn) as part of the free universal health care system in Melbourne, Australia. These groups had, in previous years, continued without nurse facilitation for approximately 18-months [36]. The Melbourne InFANT Program commenced where the MCHn involvement with the groups ceased, and parents took over their own management of the groups. The Program sessions utilized anticipatory guidance, providing information and developing skills (in anticipation of their relevance), regarding what and how to feed, active play opportunities, alternatives to screen time and restraint, and parent modelling of healthy eating, physical activity and reduced sedentary behaviours. The group format promoted discussion of strategies, successes and overcoming barriers to key messages. The control group received usual care as well as quarterly newsletters (six in total) on general child health topics not related to obesity-promoting behaviours.

Strengths of the Melbourne InFANT Program included: comprehensive assessment of targeted behaviours using gold standard methods (objective assessment of body mass index (BMI), physical activity and sedentary time, and three non-sequential 24-h dietary recalls); use of existing social groups to potentially facilitate, support and increase intervention dose by non-facilitated contacts between sessions; scalability - as the program was developed to be both low dose and community-based, allowing feasible transfer into existing public health infrastructures; high recruitment and retention rates and incorporation of an economic evaluation [24]. The Melbourne InFANT Program has been adapted for use within eight local government areas in Victoria, Australia and translation of this program from RCT to community use is currently being evaluated.

### The InFANT Extend program

The current study builds on the early outcomes of the Melbourne InFANT Program [24, 35]. This cluster randomized controlled trial will test the efficacy of an extended (33 versus 15 month) and enhanced (use of web-based materials, and Facebook® engagement), version of the original InFANT intervention in a new cohort. Outcomes at 36 months of age will be compared against the control group.

#### Primary outcomes

In comparison to the control group children, the intervention group children at 36 months of age will exhibit lower body weight and reduced waist circumference.

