### Sample size

#### Power and sample size

Child weight and waist circumference are the primary outcome measures for this study and considered the most difficult outcomes to change. Secondary aims of this intervention are to increase children’s fruit and vegetable consumption and time spent physically active, and to decrease consumption of sweetened drinks and time spent sedentary.

Australian national data [39] report an average weight and waist circumference in 3-year old children of 16.4kg (SD = 2.2kg), and 51.1cm (SD = 3.8cm) respectively [39]. Further, these data report that at this age Australian children consume an average of 85g (SD = 82g) of vegetables (not including potato), 202g (SD = 129g) of fruit and 78mL (SD = 121mL) of sweetened drinks daily. Additionally this group is reported to spend an average of 117min (SD = 30min) being active and 662min (SD = 71min) being sedentary daily [40].

To detect a 5% difference in weight between groups at age three (reducing average weight in the intervention group by approximately 1kg), with Type I and Type II errors of 5% and 20% respectively, the number of subjects required is given by:$$ \mathrm{N}\ \left(\mathrm{number}\ \mathrm{of}\ \mathrm{subjects}\right) = 32/\mathrm{E}\mathrm{S}\ {\left(\mathrm{Effect}\ \mathrm{S}\mathrm{ize}\right)}^2 $$$$ \mathrm{E}\mathrm{S} = \left(\mathrm{mean}\ \mathrm{x}\ \%\ \mathrm{meaningful}\ \mathrm{difference}\right)/\mathrm{standard}\ \mathrm{deviation} $$$$ \mathrm{So},\ \mathrm{N} = 32/0.382 = 223 $$

This sample size will also allow us to detect differences of: 4% in BMI (i.e. 0.66kg/m^2^), 3% in waist circumference (i.e. 1.5cm), 36% in vegetable consumption (i.e. 31g, equivalent to approximately ½ a serve/day); 24% in fruit consumption (i.e. 49g, equivalent to approximately 1/3 of a serve/day); 60% in sweetened drink consumption (i.e. 47mL/day); 10% in active time (i.e. 12min/day) and 4% in sedentary time (i.e. 26min/day).

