#### Primary measures

##### Child’s anthropometry

Height, weight and waist circumference will be measured by study staff who will undergo training with a paediatrician specialized in clinical nutrition. Recumbent length (in infants) will be assessed using a calibrated length mat/height and from standing age will be assessed using a calibrated stadiometer. Waist circumference (minimum circumference between the rib cage and iliac crest) will be measured using a non-stretchable tape measure at 18 and 36 months of age. BMI z score will be calculated using WHO growth standards [42].

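### Raw body weight at 36 months is one of two primary outcomes and sets the sample size, while the BMI z-score that the trial calculates has no outcome status

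*Protocol article*

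**What the plan says.** All places are in the protocol article.

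- **Primary outcomes** states the hypothesis that "the intervention group children at 36 months of age will exhibit lower body weight and reduced waist circumference".
- **Power and sample size** confirms the pair: "Child weight and waist circumference are the primary outcome measures for this study and considered the most difficult outcomes to change". It takes national figures for three-year-olds, "16.4kg (SD = 2.2kg), and 51.1cm (SD = 3.8cm", and bases the sample size on weight alone, at a 5% significance level and 80% power: "To detect a 5% difference in weight between groups at age three (reducing average weight in the intervention group by approximately 1kg". It then says that the resulting 223 subjects also suffice for "4% in BMI (i.e. 0.66kg/m^2^), 3% in waist circumference (i.e. 1.5cm".
- **Child's anthropometry**, under the Primary measures heading, adds that "BMI z score will be calculated using WHO growth standards". The BMI z-score is in neither the Primary outcomes nor the Secondary outcomes list, and BMI itself is in neither.
- **Abstract and Background** put the motivating evidence in BMI terms: earlier trials produced differences in BMI or its z-score that faded after the interventions stopped.
- **Statistical analyses** gives the model as GEE, allowing for clustering, with adjustment for baseline values where appropriate.

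**The concern.** The trial asks whether a longer programme sustains an effect on adiposity that earlier programmes lost. The outcome that fixes its size is weight in kilograms, which also varies with how tall a child is, the child's sex and the exact age at the visit. The measure that standardises for age and sex, and that matches the evidence cited, is produced but given no role.

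Two things are at stake. The first is precision: by the plan's own detectable differences weight is noisier than BMI, so a given proportional change in fatness is harder to see on weight. The second is interpretation: a result in kilograms answers the background's question less directly, and a z-score without declared status leaves its place in the report open until results are known.

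**Working it through.** **Inputs**, from Power and sample size: mean weight 16.4 kg, SD 2.2 kg; waist SD 3.8 cm; 223 effective subjects in total, split 1:1; detectable BMI difference 4%, or 0.66 kg/m²; design effect 1.8; attrition 25%.

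**Assumptions** that the article does not state: a two-sided 5% test, implied by the constant 32 because 4 × (1.96 + 0.84)² = 31.4; the same height in both arms; no gain from baseline adjustment.

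**Formulas.** N = 32/ES². Power = Φ(ES × √N / 2 − 1.96), with √223 / 2 = 7.467.

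1. *The plan's own figure.* ES = 0.05 × 16.4 / 2.2 = 0.82 / 2.2 = 0.3727. With ES rounded to 0.38, as the plan does, 32/0.38² = 221.6, close to the stated 223; unrounded, 32/0.3727² = 230.3. Inflation gives 223 × 1.8 / 0.75 = 535.2, matching 535. Power for 5% in weight is Φ(0.3727 × 7.467 − 1.96) = Φ(0.823) = 79.5%. The design does what it says for a 5% weight difference.

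2. *What the BMI figure implies.* At N = 223 the detectable effect is √(32/223) = 0.3788 SD. Implied mean BMI is 0.66/0.04 = 16.5 and implied SD is 0.66/0.3788 = 1.742. The coefficient of variation is 1.742/16.5 = 10.6% for BMI, against 2.2/16.4 = 13.4% for weight.

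3. *A 4% BMI effect carried to weight.* BMI is weight over height squared, so with height unchanged a 4% lower BMI is a 4% lower weight.
   - Weight: 0.04 × 16.4 = 0.656 kg; ES = 0.656/2.2 = 0.298; power = Φ(0.298 × 7.467 − 1.96) = Φ(0.266) = 60.5%.
   - BMI: power = Φ(0.3788 × 7.467 − 1.96) = Φ(0.868) = 80.7%.

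4. *Size needed for 80% on weight.* 32/0.298² is about 360 effective children (354 without rounding the constant up to 32), or 360 × 1.8 / 0.75 = 864 recruited (850 from 354).

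5. *Sensitivity of the 60.5%.*
   - If 4% is rounded from 3.5% to 4.5%, the weight effect is 0.574 to 0.738 kg and power is 49.5% to 70.7%.
   - Converting 0.66 kg/m² at an assumed height of 0.93 to 1.00 m gives 0.571 to 0.660 kg and power of 49% to 61%.
   - If baseline weight is adjusted for, with residual SD 2.2 × √(1 − r²), power is 65%, 73% or 79% for an assumed correlation r of 0.3, 0.5 or 0.6. This credits the adjustment to weight only; BMI could gain too.

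6. *The other primary outcome.* For waist, 1.5/3.8 = 0.395 and power = Φ(0.395 × 7.467 − 1.96) = 83.8%.

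**The case against.** The strongest reply is that weight is not the only primary outcome. Waist circumference is an adiposity measure and has about 84% power for the difference the plan names. A reader might infer from step 3 that the trial's power for any effect on adiposity falls to 60%; the article does not support that, and the figure belongs to the weight comparison alone. Waist does not fully answer the point, since it too is unstandardised for age, sex and height, and the sample size rests on weight.

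The plan also sizes on 5% in weight, where power is 79.5%. The 60% comes from applying the plan's 4% BMI difference to weight, and it needs the assumptions listed. Baseline adjustment could recover part or nearly all of the loss, depending on a correlation that the article does not give.

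Two further inferences are tempting and fail. One is that the z-score has been shown to be more powerful: the 4% is for raw BMI, no SD or target effect is given for the z-score, and 0.38 SD is what 223 subjects detect on any continuous outcome. The other is that stature, sex and age bias the weight comparison, or that a weight result could say nothing about adiposity. Randomisation makes them noise on average, already within the 2.2 kg SD, and a weight result would be read beside waist and BMI.

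Finally, a condensed article may leave covariates to the analysis plan, so silence on sex and age is not itself a fault. That stands. What remains is the choice of endpoint and the missing status of the z-score, both of which the article itself fixes.

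**Conclusion.** The point holds as one of endpoint choice, precision and interpretation. Raw weight is a primary outcome and drives the sample size, while the BMI z-score, on whose scale the rationale is built, is calculated without a declared role.

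A 4% BMI effect would have about 60% power on the weight comparison (about 50% to 71% from rounding), against about 80% on BMI, if height is unchanged and baseline adjustment brings no gain. Waist retains about 84% for 1.5 cm. Nothing can be computed for the z-score itself, and the article does not split the weight SD, so the gain from adjusting for sex and exact age cannot be computed either.

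The design is not invalid as it stands. The change is worth making because the mismatch is clear and the data are already planned.

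**What to change.** Before analysis, and while the analysts are still blinded to allocation, amend Primary outcomes and Power and sample size so that WHO BMI z-score at 36 months is the primary weight-related outcome alongside waist circumference. Move raw weight to the secondary outcomes. State the detectable difference for the z-score as about 0.38 SD at 223 effective subjects, and justify it as a plausible effect.

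If raw weight stays primary, adjust its model for sex and exact age at measurement as well as baseline weight, and give the z-score a stated secondary status. Do not adjust for height at 36 months: it is measured after randomisation, and a feeding intervention could affect it.

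No new data collection is needed, since height and weight are measured and the z-score already requires age and sex. The cost is a dated, explained change to a published protocol and a registered outcome, and a headline in z-units, which are less familiar than kilograms.

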#### Secondary outcomes

In comparison to the control group infants, the intervention group infants at 18 and 36 months of age will:Consume more serves of fruits and vegetables, and fewer serves of sugar-sweetened beverages and energy-dense snack foods;Spend more time being physically active and less time in sedentary behaviours, specifically television viewing.Exhibit improved energy-related lifestyle patterns (combining measures of diet, physical activity and screen time)

In comparison to the control group parents, the intervention group parents (when child is 18 and 36 months of age) will demonstrate:Greater knowledge regarding infant eating, physical activity and sedentary behaviours and more positive attitudes /beliefs regarding their capacity to influence these behaviours;Greater adoption of desired feeding strategies, including parental modelling of healthy eating, the division of responsibility in feeding, and increased availability of promoted (targeted) foods in the home;Greater adoption of strategies, including modelling, for increasing opportunities for physical activity and reducing opportunities for sedentary behaviours.

## Design and Methods

### Overall study design

This study will enable assessment of the effectiveness of a 33-month parent-focused child obesity-prevention intervention (compared with a no-intervention control).

Ethical approval was granted by Deakin (EC-175-2007 (Part 2- 2007–175) and the Department of Education and Early Childhood Development (Victoria, Australia) (2011_001000). This trial is registered with the Australian New Zealand Clinical Trials Registry (ANZCTR 12611000386932).

### Study participants and recruitment

The recruitment process for the InFANT Extend Program will largely replicate that used in the original Melbourne InFANT Program [24, 35]. An important exception relates to the local government area (LGA) recruitment strategy. To seek to address the over representation of university educated women in the Melbourne InFANT Program [24] seven relatively disadvantaged Victorian LGAs will be purposively recruited. These LGAs will selected by the group level variable *Index for Socio Economic Disadvantage* (IRSD) [37] such that all will be in the lowest tertile of disadvantage (i.e. most disadvantaged). It is important to note that there will be distinct areas of greater and lesser socioeconomic advantage within each LGA and these are indicated by the IRSD of postcode regions within each LGA. For practical reasons, each LGA will sit within a 75km radius of the research center (Geelong, Victoria, Australia).

Eighty percent of eligible first-time parents’ groups (rounded to next even number to ensure equal within LGA allocation to control and intervention groups) within each of these LGAs will be randomly selected and approached by research staff for recruitment during one of the standard nurse-facilitated group sessions. Individual parents will be eligible to participate if they give informed written consent, are first-time parents and are literate in English. Infants with chronic health problems likely to influence height, weight, levels of physical activity or eating habits will be excluded from analyses but will be permitted to participate in the program.

Parent groups will be eligible if eight or more parents choose to enroll in the study. To facilitate inclusion of participants experiencing disadvantage, groups commencing in MCH centres considered relatively socioeconomically disadvantaged (as determined by the post code of the region within each LGA), will be eligible if six or more parents enroll. When first-time parents’ groups decline to participate, the next randomly selected group within the LGA will be approached. Non-consenting parents within participating groups will be permitted to attend the intervention sessions, but will not be required to provide data or be contacted by the research team in any other way.

Randomization of first-time parents’ groups (clusters) to intervention or control will occur after recruitment to avoid selection bias [38]. Randomization (stratified by LGA) will be conducted by an independent statistician. While parents will not be blinded to allocation, they will not be informed of the study aims or hypotheses and the recruiting emphasis will focus on promoting healthy eating and active play from the start of life. Staff measuring height and weight will not be blinded to intervention status as they will deliver the intervention, however, data entry and analyses will be conducted with staff blinded to participant’s group allocation.

